## Abstract

**Background:**

During adolescence, individuals face various challenges that require adequate psychosocial and emotional adjustment. Additionally, the presence of a chronic illness during this stage, such as Type 1 Diabetes Mellitus (T1DM), introduces additional medical and psychological needs, which can increase vulnerability. In this context, serious games emerge as a promising tool to address educational and psychoemotional aspects while maintaining the motivation and playability typical of a video game. Currently, no technological tool simultaneously addresses both the educational and psycho-emotional needs of adolescents with T1DM.

**Aim:**

This study aims to design and validate a psychological intervention program using a technological platform that incorporates artificial intelligence. Through the serious game emoTICare, the goal is to promote physical and emotional health in adolescents with T1DM by enhancing the development of socio-emotional skills.

**Method:**

Test this tool, adolescents with T1DM will be recruited through diabetes associations across Spain. The participants, 372 adolescents aged between 12 and 16, will be randomly assigned to either a control or an experimental group. The experimental group will complete the emoTICare program. Over six weeks, participants will engage in psychoeducational activities using the tools provided by the serious game. Data Will be collected at three points: baseline (T1) and after six weeks (T2) (for the control group, T2 will be at the same time as the experimental group’s post-intervention), and aT3 (after six months of T2). The program’s effectiveness will be analyzed using various statistical packages.

**Results and conclusions:**

The study hypothesizes that adolescents will maintain or improve their physical and emotional health indicators following the emoTICare program. Specifically, statistically significant improvements (p ≤ .05) are expected in the following variables: health-related quality of life, social skills and communication, emotional awareness, resilience, self-esteem, and coping and problem-solving abilities. Additionally, a statistically significant reduction (p ≤ .05) is anticipated in variables related to the perceived threat of the disease, as well as emotional and behavioral problems. The experimental group is expected to present improvements in all these areas when comparing pre- and posttreatment evaluations, and also in comparison to the control group on the waiting list.

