### Measurements

Missing data will not be an issue, as the survey is conducted through LimeSurvey, where all questions are mandatory and cannot be skipped by participants.

To be included in the data analysis, participants must have completed all three measurement points and answered all questionnaires.

T1: First measurement: After the participant had signed the informed consent, the initial score for this outcome was assessed.T2: Second measurement: POST Up to 6 weeks after the second measurement, the second measurement of the same variable was carried out.T3: Third measurement: POST Up to 6 months after the second measurement, the third measurement of the same variable was carried out.

[Time Frame: Baseline up to 30 weeks]

Primary Outcome Measure:

Change Quality of Life (measured by KIDSCREEN-27).Change Emotional and Behavioral Problems (measured by SDQ).Change Emotional Competences (measured by EAQ-30).Change Self-concept (measured by CAG)Change Coping (measured by SPSI-R).Change Social Skills (measured by CHASO).

Secondary Outcome Measure:

Change Threat of disease (measured by BIP-Q)Change Psychoeducation Diabetes

Psychoeducation of the disease: the ECODI Diabetes knowledge scale will be used to assess this variable [79]. This scale consists of 25 items and four dimensions: basic knowledge and self-care, laboratory values, diet and physical exercise. It is a scale that is corrected by the number of hits and misses.

[Time Frame: Start of the game and during the game]

Change Resilience (measured by CD-RISC).

Other Pre-specified Outcome Measures:

Glycaemic control

HbA1c: It will be used to evaluate the glycemic control of the diabetic patient in endocrinology diseases.

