The primary focus of this study is on the evaluation of the programme’s overall effectiveness, as opposed to the presentation of definitive assertions concerning the outcomes of individual participants. It is imperative to emphasise that the tests are embedded in pre-specified models, with the primary focus being on assessing the overall effectiveness of the programme.

Before testing the change models, descriptive analyses, Pearson correlations, and multivariate and univariate analysis of variance (MANOVA and ANOVA) will be conducted using pre-intervention scores for participants in experimental and control groups to identify potential baseline differences. Furthermore, multivariate and univariate analysis of covariance (MANCOVA and ANCOVA) will be performed to detect changes in post-intervention scores (short-term effect), with pre-intervention scores as a covariate. These analyses will focus on latent variables derived from the composite scores of multiple Likert items, which represent underlying constructs such as emotional symptoms or health-related quality of life. Effect sizes (Cohen’s *d*) for each variable will also be calculated to estimate the magnitude of differences between the experimental and control groups. These analyses will be conducted using SPSS V.28.

To ensure the reliability of the results, we will begin with a series of diagnostic tests and validation procedures. This will include an analysis of residuals to assess the goodness of fit of the model, using residual plots and tests for normality (e.g., Q-Q plots and Shapiro-Wilk test). Homoscedasticity will be evaluated through the Breusch-Pagan or White’s test, and the Durbin-Watson statistic will be used to check for autocorrelation in the residuals. These tests will allow us to ensure that the assumptions of the parametric models are met. Additionally, we will conduct cross-validation (k-fold) to ensure that the model generalizes well to unseen data and is not overfitted. We will also perform outlier detection using Cook’s distance and leverage plots to examine the influence of individual data points on the model.

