Multiple hierarchical regression analyses will be conducted to examine the added predictive value of the experimental condition in explaining the intervention program’s efficacy. Hierarchical regression is a stepwise method where predictors are added to the model in blocks. The rationale behind the hierarchical approach is to assess the incremental contribution of each new block of predictors while controlling for the variables entered in the previous blocks. This allows for a clearer understanding of the unique variance explained by the experimental condition, after accounting for initial factors.

Step 1: The first block typically includes variables measured at time 1 that are believed to influence the dependent variable (i.e., the change between T2-T1 and T3-T1 for each variable). These could include baseline measures of emotional symptoms, quality of life, or disease-related factors.

Step 2: In subsequent blocks, new independent variables (predictors) are added. For example, in the second block, we would add the experimental condition (treatment vs. control) to assess its impact on the change in the dependent variable, controlling for the baseline scores. The dependent variable will be the change between pre- and post-intervention scores, as well as between pre-intervention and follow-up scores. A statistically significant change in the coefficient of determination in Model 2 (predictor: experimental condition, controlling for pre-intervention score) will be interpreted as added predictive value. A significant prediction from the experimental condition, controlling for pre-intervention score, will allow attribution of significant change to the intervention.

The Reliable Change Index (RCI) will be calculated for the scores of the evaluated variables. Reliable change will be determined by the extent to which an individual’s progress exceeds the natural fluctuation of measurements [80]. The RCI will be calculated using pre- and post-*emoTICare* means, along with the pre-intervention standard deviation and Cronbach’s alpha index.

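### Six co-equal primary instruments are each judged at p ≤ .05, with change tested at two follow-ups and no rule that holds the overall false-claim rate at 5%

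*Protocol article*

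**What the plan says.** The Measurements section lists six primary outcomes: "Change Quality of Life (measured by KIDSCREEN-27" opens the list, followed by "Change Emotional and Behavioral Problems (measured by SDQ).Change Emotional Competences (measured by EAQ-30", self-concept by the CAG, then "Change Coping (measured by SPSI-R).Change Social Skills (measured by CHASO". They are not ranked and no time point is marked as primary. Disease threat (BIP-Q), diabetes knowledge and resilience (CD-RISC) are secondary.

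The Abstract (Results and conclusions), the Objectives and the end of Data analysis all set the threshold variable by variable: "Specifically, statistically significant improvements (p ≤ .05) are expected in the following variables", and likewise "a statistically significant reduction (p ≤ .05) is anticipated in variables related to the perceived threat of the disease". These lists include resilience and disease threat, so two secondary outcomes stand at the same threshold as the primary ones. They also speak of self-esteem where the primary outcome is self-concept.

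The Data analysis section then plans:
- MANCOVA and ANCOVA on post-intervention scores, adjusted for the pre-intervention score and described as the short-term effect, which is T2.
- Hierarchical regression on "the change between T2-T1 and T3-T1 for each variable", restated as "The dependent variable will be the change between pre- and post-intervention scores, as well as between pre-intervention and follow-up scores". A significant prediction from the experimental condition, given the pre-intervention score, allows the change to be attributed to the intervention.

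The only wording near multiplicity says that the tests sit in pre-specified models, with "the primary focus being on assessing the overall effectiveness of the programme".

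**The concern.** The threshold, the six equal primaries, the two contrasts and the attribution rule are all stated. Followed as written, they allow a causal claim for any one outcome that reaches .05 at either follow-up. Nothing says how many outcomes must succeed, which time point counts, or whether the multivariate test must be passed first. A programme with no effect on anything would then have much more than a 5% chance of producing at least one result reported as an effect.

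Two features add to this. For four instruments the score to be analysed is not fixed. And ANCOVA and the change-score regression may look like two independent lines of evidence when, with the same covariate, they are one.

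**Working it through.** **Plan's own figure.** The protocol states no familywise error rate and no power, so there is none to reproduce. Its one computed design figure, 372 participants, is used below only as a head count.

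**Inputs from the protocol.** Six primary instruments; .05 per variable; two contrasts per variable (T2-T1 and T3-T1). **Assumed.** Two-sided tests, because sidedness is not stated, and a range of correlations between test statistics, because none is given.

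**Independent tests.** Chance of at least one false positive among k tests = 1 − 0.95^k.
- k = 6: 1 − 0.95^6 = 0.265
- k = 12 (6 × 2): 1 − 0.95^12 = 0.460

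**Correlated tests.** For k equally correlated normal statistics, numerical integration gives:

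| Tests | Independent | Correlation 0.5 | Correlation 0.7 |
|---|---|---|---|
| 6 (one time point) | 26% | 21% | 16% |
| 12 (two time points) | 46% | 32% | 23% |

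The same adolescents are measured at T2 and T3, so full independence of twelve tests is implausible. A 6 × 2 structure, with correlation 0.3 to 0.7 between instruments and 0.5 to 0.7 between time points, gives 26% to 40% by simulation.

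**False claims of benefit only.** With two-sided tests, half of each .05 lies in the favourable direction. If independent: 1 − 0.975^6 = 0.141 and 1 − 0.975^12 = 0.262.

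**Would MANCOVA protect if it were made a gate?** Only when no outcome is truly affected. If one outcome truly improves and opens the gate, the other five are each tested at .05: 1 − 0.95^5 = 0.226 if independent. The T3 regressions lie outside it in any case.

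**Open score.** The assessment tools section names an overall score for SDQ (Total Difficulties) and CAG (global self-concept). KIDSCREEN-27, EAQ-30, SPSI-R and CHASO are described by 5, 6, 5 and 10 subscales with no total named. If every subscale of those four were tested, with the two totals, there would be 5 + 6 + 5 + 10 + 2 = 28 scores. At one time point the error would then be 1 − 0.95^28 = 0.76 if independent, or about 0.49 at correlation 0.5. This is conditional: the protocol does not say that subscales will be tested.

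**Two models, one test.** The regression is (Y2 − Y1) = a + b·arm + c·Y1. Moving Y1 across gives Y2 = a + b·arm + (c + 1)·Y1, which is the ANCOVA. The coefficient b, its standard error and its p-value are the same.

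**Power under the fix.** The Sample size section gives 372 participants and 20% dropout: 372 × 0.8 = 297.6, about 149 per arm. The strictest Holm step is .05/6 = .0083. For a two-sample comparison:
- effect detectable with 80% power: d = 0.33 at .05, d = 0.41 at .0083
- power at d = 0.5: 99% at .05, 95% at .0083

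**The case against.** The best defence has four parts.

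- *The adjustment belongs in the analysis plan, which is not shown.* Silence on the method alone would be no finding. Here the protocol states the per-variable threshold and the attribution rule, and a later plan would have to override them.
- *There is an overall test.* MANCOVA is a joint test of arm across outcomes, so it would be wrong to say that no overall test is planned. But it is not made a condition for the univariate tests or the regressions.
- *The authors expect gains in every listed area.* If success on all primaries were required, the error could not exceed 5%. The text states an expectation, not a decision rule, and the attribution rule works one variable at a time.
- *The outcomes are correlated.* They are, and this lowers the error. Even at correlation 0.7, six tests give 16%.

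Four stronger readings are tempting, and the documents do not support them:

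- A reader might take 21% to 46% as the trial's error rate. The lower figure is six correlated tests at one time point, the upper is twelve independent tests. They are different scenarios, not a range for one.
- A reader might count all 37 subscales at two time points as 74 tests. Data analysis speaks of composite scores without saying which, and EAQ-30 and CHASO each carry a single overall alpha. Subscale testing is possible, not stated.
- A reader might count MANCOVA, ANCOVA and regression at both time points as separate sources of error. MANCOVA and ANCOVA concern the short-term effect; T3 change appears only in the regression. Where ANCOVA and regression coincide they add no error. The first regression block may hold further baseline variables, and then they need not coincide exactly.
- A reader might conclude that the trial cannot support any claim of effectiveness. It can, once a rule is fixed.

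**Conclusion.** The point holds. With six unranked primary instruments, .05 for each, two change contrasts and a variable-by-variable attribution rule, the familywise error exceeds 5% in every scenario examined. How far it exceeds 5% depends on correlations, sidedness and the choice of scores, none of which the protocol gives, so the percentages above are illustrations and not bounds. Subscale testing of the four instruments without a named total would raise them further. Agreement between ANCOVA and the change-score regression with the same baseline covariate should not be presented as confirmation.

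**What to change.** In Measurements and Data analysis:

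1. Name one score for each primary instrument.
2. Make T2 the primary time point.
3. Make one baseline-adjusted ANCOVA per outcome the confirmatory test.
4. Apply Holm across the six p-values. The alternative is to nominate one primary outcome and treat the other five as ordered secondaries.
5. Label T3, subscales, BIP-Q, CD-RISC and the hierarchical regressions secondary or exploratory.
6. Limit the attribution rule to between-arm differences that are significant after Holm, and bring the hypotheses in the Abstract and Objectives into line.

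The cost is one paragraph and some sensitivity. At the strictest Holm step the effect detectable with 80% power rises from about d = 0.33 to about 0.41. Power remains about 95% if the protocol's moderate effect means d = 0.5 and about 149 per arm are analysed after 20% dropout; both are assumptions. The change should be made before any between-arm result is seen. Table 1 schedules preliminary analysis from January 2026, while T3 data are still being collected.

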## Introduction

Adolescence is a developmental stage characterised by significant physiological, social and psychological transformations [1]. This period is characterised by a combination of challenges and opportunities, as young individuals commence the process of defining their identities [2] and assuming an increasing array of responsibilities [3,4]. These transitions can be particularly challenging for adolescents [5,6], with the potential to have a significant impact on their quality of life and psychological well-being [7].

The presence of a chronic illness (CI) can further compound the challenges faced by adolescents [8,9]. According to the World Health Organization (WHO), the most prevalent chronic diseases include cardiovascular conditions, cancer, chronic respiratory diseases, and diabetes [10]. Of these, Type 1 Diabetes Mellitus (T1DM) is a particular focus, given its propensity to emerge during childhood and adolescence, although it can develop at any age [11]. T1DM is the most prevalent chronic endocrine disorder during childhood [12–15] and remains one of the most frequent chronic illnesses in adolescence [16–18]. The incidence of T1DM is highest during preadolescence and adolescence, especially between the ages of 10 and 14–15 [2,11]. In 2021, the global incidence of T1DM among children and adolescents under 15 was 651,700 cases, with 108,200 new cases reported annually. This upward trend is attributable to elevated incidence rates and reduced mortality [19].

The underlying pathophysiology of T1DM is the destruction of pancreatic β-cells, resulting in a deficiency in insulin production [11,15,20]. The management of this condition necessitates rigorous blood glucose monitoring, insulin therapy, diabetes education, medications, regular physical activity, and dietary control [21,22]. Without adequate management, T1DM can lead to complications affecting various organs and systems, increasing the risk of severe and potentially life-threatening conditions [2,23]. Furthermore, the impact on the quality of life of adolescents with T1DM is significant [17].

The challenges associated with Type 1 Diabetes Mellitus (T1DM) extend beyond the physical health domain, as the condition has also been linked to a range of psychosocial difficulties experienced during adolescence [20]. Research has demonstrated that robust social and family support networks, in conjunction with a positive self-concept, can function as protective factors for adolescents with T1DM [24]. Furthermore, research indicates that more than 25% of children and adolescents diagnosed with chronic illnesses such as diabetes also have a diagnosed mental health condition [25], which increases their vulnerability to psychological disorders [26]. Emotional difficulties such as depression [27,28] and anxiety [6,7,29–31] are more prevalent among young people with diabetes. The presence of a chronic illness during adolescence has been associated with emotional and behavioural problems [9], as well as a decline in quality of life [20], both of which can interfere with treatment adherence and raise the risk of complications.

Adolescents diagnosed with chronic conditions such as T1DM have been observed to respond with denial or resistance to treatment [32]. Furthermore, as previously mentioned, adolescence is a period of increased risk-taking behaviours, which can lead to non-adherence to treatment plans and further exacerbate the likelihood of complications [6,17]. Given that there is currently no cure for T1DM, treatment is primarily aimed at improving quality of life, minimising risk factors, and reducing the number of complications [7,10,24].

The treatment of adolescents with diabetes is not solely focused on the delivery of medical care; rather, it is a multifaceted approach encompassing a range of indicators, including health-related quality of life [33–36] and physical and socio-emotional well-being [37–39]. Empirical evidence has demonstrated the efficacy of psychological interventions that cultivate emotional intelligence and assertive communication in enhancing well-being and quality of life in individuals with T1DM [40,41]. Such treatment programmes typically encompass domains such as adapting to the diagnosis, fostering emotional awareness and regulation, cultivating problem-solving skills, mitigating negative thought patterns and worry, nurturing positive beliefs, reducing psychological symptoms (particularly anxiety, depression and behavioural issues), and fortifying identity, self-concept and social skills.

In this context, information and communication technologies (ICTs) have emerged as effective tools for addressing various psychological and emotional needs [42]. Among these, serious games—defined as games or activities designed for purposes beyond entertainment, such as teaching skills or concepts [43,44]—have gained popularity. These tools are widely utilised in educational and therapeutic settings due to their interactive nature, which fosters high motivation and engagement [45,46]. In the realm of psychological interventions, these games have been incorporated to enhance patient understanding of chronic illnesses and promote emotional adjustment [43,47].

In the context of this study, serious games developed for children and adolescents with T1DM have proven effective in facilitating meaningful learning. These games have been shown to convey crucial knowledge about the condition, support skill development, and enhance motivation and self-efficacy, all of which have a positive impact on adjustment to living with T1DM [48].

### Objectives

The main objectives of this study are: (1) to design and implement a *serious game* called *emoTICare* to promote physical and emotional health, as well as the development of socio-emotional skills among adolescents with Type 1 Diabetes Mellitus (T1DM) through a psychological intervention conducted on a technological platform that incorporates artificial intelligence and Ecological Momentary Assessment (EMA); (2) to analyze the effectiveness of this *serious game* on indicators of disease adjustment, quality of life, and socio-emotional well-being, as well as improvements in socioemotional competencies and skills.

The study hypothesizes that adolescents will maintain or improve their physical and emotional health indicators following the *emoTICare* program. Specifically, statistically significant improvements (*p* ≤ .05) are expected in the following variables: health-related quality of life, social skills and communication, emotional awareness, resilience, self-esteem, as well as coping and problem-solving abilities. Additionally, a statistically significant reduction (*p* ≤ .05) is anticipated in variables related to the perceived threat of the disease, as well as emotional and behavioral problems. The experimental group is expected to show improvements in all these areas when comparing pre- and post-treatment evaluations, and also in comparison to the control group on the waiting list.

